### Hypotheses

The primary hypothesis is that MP rate and intensity in the intervention group will reduce, compared with the controls. Also, the secondary hypothesis is that the intervention group will modify their posture behavior, compared with the control group.

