### Outcomes and measures

The participants will complete a short demographic characteristics form containing items about age, gender, grade, instrument type, and weekly playing time. The primary outcomes are:The presence of MP, which is assessed using the Nordic Body Map (NBM) questionnaireThe intensity of pain that will be evaluated via a numerical rating scale (NRS) questionnaire, wherein the participants are asked to circle the number between 0 and 10 that fits best to their pain intensity. Also, zero represents “no pain at all” whereas pain ratings between 1 and 3 indicate mild pain, 4 to 6 show moderate pain, and 7 to 10 denote severe pain

To collect these self-reported data, a link to the online questionnaire is posted in two WhatsApp groups supervised by the class teacher. In addition, there are no missing data due to the obligation to answer all questions.

The secondary outcome takes account of posture behavior, estimated through the Rapid Entire Body Assessment (REBA) tool by observing and filming the body positions of the music students during specific postures while playing a musical instrument through the SHAD platform. One independent trained rater blinded to the study will also observe and record the participants’ postures. Each posture is initially given a score. Then, the posture scores are estimated based on the diagram shown in Fig. 1. The final REBA score will be between 1 and 15 and divided into five levels in terms of risks: 1 = negligible risk, 2–3 = low risk, 4–7 = moderate risk, 8–10 = high risk, and 11–15 = very high risk [31].

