**Fig. 1 Fig1:**
[figure not shown]
Rapid Entire Body Assessment (REBA) score sheet (Ahmadi et al. 2015)

The participants’ data are collected at two points in time, namely, at baseline (1 week before the educational program) and 6 months after it. To prevent attrition and bias, the data are collected from all participants and included in the data analysis, regardless of adherence to the study protocol. The participants will also receive a small gift for their participation.

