### Statistical analysis

The data will be analyzed using the SPSS Statistics software package 24.0 (IBM SPSS 24.0 Ink, NY: IBM Corp). All continuous variables will be also assessed for their normal distribution. *T*-test, Mann-Whitney *U* test, and chi-square test will be then utilized to compare the baseline measurements. The descriptive statistics are also reported to investigate the data. To obtain the time period (at baseline and 6-month evaluation, as the test time factor) in which the difference in mean scores within the groups (viz. group factor) originates, the two-way analysis of variance (ANOVA) will be exploited. The test for homogeneity of the data is further employed for the between-participant variables. Since we do not have a variable with more than one pair, confidence interval adjustment is not selected. The Wilcoxon signed-rank test is additionally calculated for the difference in the MP rate between both study groups. Moreover, the effect sizes will be calculated using the partial eta-squared measure (ηp^2^) that gives the idea of how different the participants are. The significance level will be set at *p* < 0.05.

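### The time-by-group ANOVA for mean scores leaves the treatment term unnamed and uses the baseline less efficiently than a baseline-adjusted 6-month comparison

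*Protocol article*

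**What the plan says.** The Hypotheses section of the protocol article states both aims as comparisons between arms: "MP rate and intensity in the intervention group will reduce, compared with the controls", and "the intervention group will modify their posture behavior, compared with the control group".

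Outcomes and measures makes pain intensity on the 0–10 NRS a primary outcome and posture on REBA the secondary one ("The final REBA score will be between 1 and 15"). Data are collected "at baseline (1 week before the educational program) and 6 months after it".

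Statistical analysis does the following with scores:

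- It compares the arms at baseline by significance tests ("chi-square test will be then utilized to compare the baseline measurements").
- It plans a two-way ANOVA whose time factor has two levels ("at baseline and 6-month evaluation, as the test time factor"). Its purpose is to find the period "in which the difference in mean scores within the groups (viz. group factor) originates, the two-way analysis of variance (ANOVA) will be exploited".
- It names partial eta-squared for effect sizes.

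It names neither NRS nor REBA beside the ANOVA. The link is an inference from the reference to mean scores, because these are the only scored outcomes described; the pain rate is given a separate test.

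**The concern.** The question put to the ANOVA is phrased as a difference inside the groups, whereas the trial asks about a difference between them. A two-way time-by-group ANOVA yields three tests: time, group, and their interaction. The section does not say which of them decides whether the intervention worked. The three answer different questions and have very different power, so for a primary outcome the choice should not remain open until the output is seen.

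Two further points follow from what the text does fix. First, each student's baseline enters only as a level of the time factor and as the object of significance tests, not as a covariate, although it is already collected and could sharpen the 6-month comparison. Second, partial eta-squared has no direction and is not in NRS or REBA units, so it does not tell a reader how much pain or posture risk changed.

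**Working it through.** **Inputs from the protocol article.** Sample size section: p1 = 0.44, p2 = 0.30, two-sided α = 0.05, power 80%, 185 per group, 204 per group after 10% dropout.

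**Inputs assumed.** The article gives no standard deviation, effect or correlation for NRS or REBA. I therefore assume equal variance σ² at both visits, a baseline-to-6-month correlation ρ between 0.2 and 0.8, and an effect that gives exactly 80% power when 6-month values alone are compared. Clustering by class is ignored throughout.

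**The plan's own figure.** With the article's formula, n = (1.960 + 0.842)² × [0.44×0.56 + 0.30×0.70] / 0.14² = 182.8, so 183; the pooled version gives 186. At 185 the power is 0.799. For dropout, 183/0.9 gives 204, as does 185 × 1.1; 185/0.9 gives 206. The stated figures reproduce to within a few students. They concern pain prevalence, so this point does not touch them; I use 185 only as a realistic number per arm.

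**Reference effect.** d = (1.960 + 0.842) × √(2/185) = 0.291 SD, so the non-centrality for 6-month values alone is 2.802.

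**Variance of each contrast, in units of 2σ²/n:**

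- 6-month values alone: 1
- Repeated-measures group-by-time interaction (with two visits, the between-arm difference in change): 2(1−ρ)
- Baseline-adjusted 6-month difference (ANCOVA): 1−ρ²
- Group main effect (average of the two visits): (1+ρ)/2, with the effect halved to d/2, because no effect can exist at baseline

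The ratio of interaction to ANCOVA variance is 2(1−ρ)/[(1−ρ)(1+ρ)] = 2/(1+ρ). It exceeds 1 for every ρ below 1.

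**Power** = Φ(non-centrality/√variance − 1.96), with non-centrality 2.802, or 1.401 for the main effect. For example, at ρ = 0.3 the interaction gives 2.802/√1.4 − 1.96 = 0.408, power 0.66; ANCOVA gives 2.802/√0.91 − 1.96 = 0.977, power 0.84; the main effect gives 1.401/√0.65 − 1.96 = −0.22, power 0.41.

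| ρ (assumed) | Variance ratio 2/(1+ρ) | Interaction | ANCOVA | Group main effect |
|---|---|---|---|---|
| 0.2 | 1.67 | 0.60 | 0.82 | 0.44 |
| 0.3 | 1.54 | 0.66 | 0.84 | 0.41 |
| 0.5 | 1.33 | 0.80 | 0.90 | 0.37 |
| 0.7 | 1.18 | 0.95 | 0.975 | 0.33 |
| 0.8 | 1.11 | 0.99 | 0.997 | 0.31 |

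The 6-month-only comparison stays at 0.80. Below ρ = 0.5 the interaction is therefore less powerful than ignoring the baseline altogether; at ρ = 0.5 it equals it; above that it gains, but never reaches ANCOVA.

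**The case against.** The best defence is that the ANOVA, loosely worded, is a standard mixed repeated-measures model. The section speaks of a time factor and a group factor, and applies its homogeneity check to variables described as between-participant, which implies a within-participant factor; time is the only candidate. With two visits, the interaction is the between-arm difference in change, and under randomisation it has the same expectation as the 6-month difference. Naming the model term and the error structure is often left to a full protocol or SAP, which are not shown. Analysing change is a valid choice, even if not the most efficient one.

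Most of this stands, and it rules out three stronger readings that a reader might draw:

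- *That the two visits are analysed as independent observations, making the test invalid.* The article does not call the model repeated-measures, but nothing in it asserts independence, and the between-participant wording points the other way.
- *That the ANOVA cannot address the between-arm question.* It can, through the interaction. What is missing is a statement that the interaction is the test; no wrong contrast has been shown. Likewise, nothing says that the group main effect will be used.
- *That the baseline is wasted and chance imbalance left uncorrected.* A change contrast uses each student's baseline and subtracts any imbalance, though less efficiently than regression adjustment does. Nor can one say that there are few classes: the Randomization section gives no number.

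The defence does not remove the rest. The stated purpose of the ANOVA concerns differences within groups, the only effect measure named is unitless, and even the most favourable reading is less precise than adjustment for a baseline that is already in hand.

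**Conclusion.** The point holds as an avoidable inefficiency combined with an unnamed treatment term, not as an invalid analysis. Read as a repeated-measures interaction, the planned test is a legitimate between-arm comparison whose variance is 2/(1+ρ) times that of the baseline-adjusted analysis: about a third larger at ρ = 0.5, a little over half larger at 0.3, and 18% larger at 0.7. In power this is a loss of roughly 18, 10 and 2 percentage points at ρ = 0.3, 0.5 and 0.7, so the gain from changing is large only if the correlation is modest. The more damaging figure, about 0.4 or lower, applies only if the group main effect is taken as the treatment test, which the wording neither states nor excludes.

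The variance ratio depends on equal variances at the two visits. The power values further depend on the assumed ρ, on an effect chosen to give 80% power, and on ignoring clustering. They compare methods and are not estimates of this trial's power. That the ANOVA applies to NRS and REBA is an inference. The prevalence-based sample size is unaffected.

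**What to change.** For NRS and REBA, state that the primary estimate is the between-arm difference in mean score at 6 months, with a 95% CI, adjusted for the student's own baseline value and for the matching factors grade and gender. Fit it in a model that respects allocation by class, for example a linear mixed model with a class random effect. Report this difference in scale units rather than relying on partial eta-squared. Show baseline data descriptively, without significance tests.

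If the ANOVA is kept, the least change is to say that it is repeated-measures, to name the group-by-time interaction as the test of the intervention, and to give the between-arm difference in change with its CI.

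The cost is a rewording of the analysis section. Both measurements are already planned, and grade and gender are already recorded and used for matching.

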## Methods

### Trial design

This study is a matched-pair, two-arm, parallel randomized superiority-controlled trial (RCT), which will be conducted at the Tehran Conservatory of Music, Tehran, Iran, in the 2021–2022 school year. The educational intervention is presented through the web-based Student Education Network (with the acronym, SHAD), initiated by the Ministry of Education to pave the way for sustaining the process of education and learning in the country amid the COVID-19 outbreak.

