### Sample size

Sample size calculation is based on the study by Mehrparvar et al. (2012) on MP among Iranian instrumentalists [9], wherein the prevalence of MP in music students had been reported about 44% (p1 = 0.44). If it is assumed that the given rate will decrease to 30% (p2 = 0.30) after the El-Poems intervention, a trial consisting of 185 music students per group would have 80% power (*β* = 0.2) at the 5% significance level (*α* = 0.05). To assume a 10% dropout for each group, at least 204 samples in each group will be needed for the El-Poems study. The following formula is accordingly applied to calculate the sample size:$$n=\left\{{\left({Z}_{1-\upalpha /2}+{Z}_{1-\upbeta}\right)}^2\times \left[{p}_1\left(1-{p}_1\right)+{p}_2\left(1-{p}_2\right)\right]\right\}/{\left({p}_1-{p}_2\right)}^2$$

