### Randomization

Totally, there are two national music conservatories in Tehran, Iran. Since individual allocation is not possible in a conservatory’s context, the classes at each conservatory are first randomly divided into two matched groups based on the number of students, grade, and gender. Then, the groups are numbered as 1 and 2 and placed in the bowl. A neutral person is next asked to pull out one of the numbers from the bowl. The group number 1 is thus assigned to the intervention group and 2 is given to the controls. The main researcher also supervises the randomization steps. The current RCT protocol is reported in compliance with the Consolidated Standards of Reporting Trials (CONSORT) guidelines. The El-Poems study flowchart is depicted in Fig. 2.

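### The between-group difference in musculoskeletal pain rate is assigned a paired test (Wilcoxon signed-rank), but the protocol defines no pairs across the arms

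*Protocol article*

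**What the plan says.** All references are to the Protocol article.

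- Hypotheses: "The primary hypothesis is that MP rate and intensity in the intervention group will reduce, compared with the controls". This is a contrast between arms.
- Outcomes and measures: presence of MP on the Nordic Body Map is one of two primary outcomes; the other is pain intensity on a 0–10 scale. Data are collected twice, "namely, at baseline (1 week before the educational program) and 6 months after it".
- Sample size: the control rate is taken as 44% and it is assumed that "the given rate will decrease to 30% (p2 = 0.30) after the El-Poems intervention". The formula is the one for two independent proportions.
- Trial design: "This study is a matched-pair, two-arm, parallel randomized superiority-controlled trial (RCT". The Randomization section describes the matching: "the classes at each conservatory are first randomly divided into two matched groups based on the number of students, grade, and gender". One of the two groups is then drawn for the intervention.
- Statistical analysis: "The Wilcoxon signed-rank test is additionally calculated for the difference in the MP rate between both study groups". In the same paragraph, the t-test, Mann-Whitney and chi-square tests are assigned to baseline comparisons, and a two-way ANOVA (time and group) is assigned to mean scores.

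**The concern.** The sentence on the MP rate names a between-group difference and gives it a test that works on paired differences. The students in the two arms are different people, and nothing in the protocol links a student in one arm to a student in the other. An analyst following the sentence must either test before–after change inside each arm, which answers a different question, or invent a pairing.

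MP presence is the outcome on which the trial was sized. As written, the document names no suitable test of the arm effect on it. Separate before–after tests also invite the reading that significance in one arm and not in the other shows an effect, and that reading does not control the error rate of the between-arm claim.

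**Working it through.** **1. What the trial was sized for.** Inputs from the Sample size section: p1 = 0.44, p2 = 0.30, two-sided α = 0.05, power 80%.

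n = (1.960 + 0.842)² × [0.44 × 0.56 + 0.30 × 0.70] / 0.14² = 7.849 × 0.4564 / 0.0196 = 182.8, so 183 per group. The stated 185 is within 2 of this; the pooled-variance version gives 186. For 10% dropout, 183 / 0.90 = 203.3, so 204, as stated (185 × 1.1 = 203.5 also rounds up to 204). The calculation therefore reproduces as a comparison of two independent groups. No paired design enters it.

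**2. What pairs exist.**
- Student to student across arms: none defined.
- Class to class across arms: the classes are split into two matched groups. No list of class pairs, number of classes or class-level analysis is given.
- Baseline to 6 months in the same student: yes, within each arm.

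**3. What the signed-rank test does with yes/no data.** Each paired difference is −1, 0 or +1, and zeros are dropped. With b differences of +1, c of −1 and m = b + c, every non-zero difference has the tied rank (m + 1)/2. The signed rank sum is (b − c)(m + 1)/2 and its null variance is m(m + 1)²/4, so z = (b − c)/√(b + c). That is the sign or McNemar statistic. On before–after pairs it tests change over time in that arm, and the other arm does not enter it.

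**4. Illustration with no intervention effect.** Two simulations were run without class clustering. The drift and the within-person correlation are assumptions; the documents give neither.

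| Change in both arms | Within-person correlation | Significant in intervention arm | Significant there, not in control | Between-arm chi-square |
|---|---|---|---|---|
| 44% to 44% | latent 0.3 / 0.6 / 0.8 | 5.4 / 5.8 / 5.0% | 5.2 / 5.6 / 4.8% | 5.2 / 5.6 / 5.4% |
| 44% to 37% | latent 0.3 / 0.6 / 0.8 | 34 / 42 / 58% | 23 / 25 / 27% | 5.3 / 5.0 / 5.1% |
| 44% to 36% | phi 0.4 | 55% | 27% | not run |
| 44% to 30% | latent 0.3 / 0.6 / 0.8 | 87 / 95 / 99% | 11 / 5 / 1% | 5.2 / 5.1 / 4.4% |

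The 36% row used 184 per arm and 1,000 runs; the others used 185 per arm and 4,000 runs. The third column is power to detect a real change over time, not a false-positive rate of the signed-rank test. The fourth column is an error rate only if that pattern is read as an intervention effect.

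**5. Pairing students across arms by row order.** Over repeated trials this holds about 5% under the null (4.6% to 5.5% in the same runs) and has about 80% power at 0.30 versus 0.44. For any one data set, however, the answer depends on an arbitrary ordering. With 56/185 versus 75/185 (chi-square p = 0.039), the signed-rank p ranged from 0.018 to 0.064 over 5,000 orderings.

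**The case against.** The strongest defence is the matched-pair label. A reader might infer from the criticism that the signed-rank test can never compare two arms. That would be wrong: it is a paired test, not necessarily a within-person one, and it could validly compare the MP rates of matched classes, one in each arm. The label is probably why it was named. What stands against this defence is that the Randomization section stops at two matched groups and defines neither the class pairs nor an analysis of them. At least 6 pairs would be needed for two-sided p < 0.05 to be attainable at all (2/2⁶ = 0.031; 5 pairs give 2/2⁵ = 0.0625), and the number of classes is not given.

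A second defence concerns size. A reader might take the 55% or the 27% as the trial's type I error. The documents do not support that: they state no rule that significance in one arm only means success, and they give no common drift. The one related figure, from the pilot study cited in the Background, has control pain scores rising by 8%, although that is a score and not a rate. Without drift there is no inflation. This objection is accepted, and the simulation is illustrative only.

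A third defence is that the test is an addition to the ANOVA, partial eta-squared and descriptive statistics, and that an article may leave effect measures and intervals to a fuller document. This is true, and pain intensity does have an analysis named for it. But the ANOVA is stated for mean scores, so the signed-rank test remains the only one named for the MP rate between groups. The problem is a rule stated wrongly, not a detail left out.

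**Conclusion.** The point holds in this form: a paired test is assigned to a between-arm contrast for which no pairs across arms are defined, on the primary outcome that determined the sample size. This follows from the protocol's own text and needs no assumption.

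The numerical consequence does need assumptions. If both arms drifted from 44% to about 36–37% and significance in the intervention arm alone were read as an effect, the false-positive rate would be roughly 23–27%. It would be about 5% with no drift, and 1–11% with a drift to 30%, because then both arms usually become significant.

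It does not follow that the signed-rank test is unusable in any matched design, or that the trial has no analysis for any primary outcome.

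**What to change.** Replace the sentence with a between-arm comparison of MP presence at 6 months, adjusted for baseline MP (for example logistic regression), reporting a risk difference or odds ratio with 95% CI.

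Because the Randomization section allocates whole classes, the model should also account for class, by a mixed model or by GEE with a small-sample correction if classes are few. A plain chi-square test would remove the pairing error but still ignore the allocation by class. If a class-pair analysis was intended, the pairs and their number should be stated.

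The cost is one paragraph of text, no new data and slightly more analysis work. The planned numbers still match the contrast: before any allowance for class, an unadjusted comparison of 0.44 with 0.30 has power 79.9% at 185 per arm and 83.6% at 204. Accounting for class will probably widen the intervals.

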### Timeline

Table 1 shows the timeline for each session and task in the intervention, as well as who performs each task.

The study limitations are also related to the nature of e-learning interventions. In the face-to-face learning, educators can control the instruction dosage by leading learners through training sessions. E-learning interventions, however, do not allow educators to transmit the content straightly, so they have to control the dosage. In the El-Poems study, there were attempts to address this limitation by asking the participants about the content and monitoring the amount of their attention to the program through the question & answer method (Q&A). Secondly, the lack of group discussion will be another limitation, associated with the nature of e-learning interventions. The group discussion is a very important method for the success of such interventions [33]. However, in the El-Poems study, opportunities for discussion, reflection, and participant engagement with the educators will be considered, where the participants are requested to share their questions, thoughts, and experiences about proper posture, MP, and the intervention.

## Conclusion

It is concluded that music conservatories in Iran need to receive prevention programs in order to enhance proper posture behavior and reduce MP among music students. Therefore, interventions that can target posture behavior at conservatories, with enough feasibility in the long run, should be implemented. The El-Poems study can be thus an available health promotion intervention, particularly during the COVID-19 pandemic.

